### Outcome Measures

The primary outcome is the onset of PE after study inclusion. The secondary outcomes are the following maternal and fetal adverse outcomes: maternal death, pulmonary edema, acute renal failure, cerebral hemorrhage, cerebral thrombus, disseminated intravascular coagulation, eclampsia, HELLP syndrome, rupture of placenta, placental abruption, perinatal death, stillbirth, intrauterine growth restriction, small for gestational age, respiratory distress, necrotizing enteritis, intraventricular hemorrhage or subdural and cerebral hemorrhage, neonatal hypoxic encephalopathy, or periventricular leukomalacia. In addition, the date and mode of delivery, fetal weight, and Apgar score are important outcome measures.

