### Recruitment

Potential participants will be identified by the research team from the antenatal clinic at Women’s Hospital, School of Medicine, Zhejiang University. Eligible women must meet all inclusion criteria without violating any of the exclusion criteria (Textbox 1) and will be provided with the participant information and consent form to sign. A research team member will provide a verbal explanation of the trial, including a description of the trial processes, the voluntary nature of the trial, and that a decision of whether or not to participate will not affect normal clinical care. No trial-related procedures will be performed on any individual without their prior written informed consent. All participants will be followed up until 42 days postpartum.

Inclusion and exclusion criteria for determining trial eligibility.Inclusion criteriaAged ≥18 years.Gestational week 20+0 to 33+6.Signed written informed consent.Single pregnancy.Clinically suspected preeclampsia (PE), meeting one or more of the following criteria:(i) new onset of elevated blood pressure (systolic ≥130 mmHg and/or diastolic ≥80 mmHg);(ii) aggravation of preexisting hypertension (increase of more than 30 mmHg systolic/15 mmHg diastolic from the basic blood pressure in patients without hypertension, or a significant increasing trend or increase beyond the controlled level based on the original treatment for patients with hypertension);(iii) new onset of proteinuria (no urinary tract infection);(iv) one or more clinical symptoms indicate suspected PE (other possible causes have been ruled out): upper abdominal pain, headache with impaired vision, fetal growth restriction, thrombocytopenia (platelets count<100×10^9^/L), liver function impairment (elevated blood concentrations of liver transaminases up to twice the normal concentration), and renal impairment (serum creatinine>1.1 mg/dL or a doubling of the serum creatinine concentration in the absence of other renal disease).Exclusion criteriaConfirmed diagnosis of PE/chronic hypertension with PE (superimposed PE).Confirmed diagnosis of eclampsia.Confirmed diagnosis of hemolysis with a microangiopathic blood smear, elevated liver enzymes, and low platelets (HELLP syndrome).Fetal chromosomal abnormalities.Concomitant participation in another clinical study.Received investigational intervention drugs in the past 3 months.Visible hematuria.Preexisting renal disease.

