### Selection of Predictor Variables

According to the objective of this study, the misfolded protein level in urine will be considered as a predictor candidate for PE onset or adverse outcomes. Other preset variables include: (1) demographic factors, including high-risk factors of PE; (2) urine biomarkers reported in the literature; (3) medication; and (4) routine clinical variables or laboratory tests in daily practice (Textbox 2). The determination of valid variables will be based on the statistical analysis results with a significance level of *P*<.05.

Preset variable candidates for model development.Demographic factorsAgeBMIConception modeParityPreexisting hypertension, diabetes, autoimmune diseases (systemic lupus erythematosus, antiphospholipid syndrome)Urine biomarkersMisfolded proteinsPlacental growth factorSoluble FMS-like tyrosine kinase 1Total proteinCreatinineMedicationAspirinAntihypertensive drugsRoutine clinical variables or laboratory testsBlood pressureAspartate aminotransferaseLactate dehydrogenaseSerum creatinineProteinuria (spot urine protein, 24-hour urine protein)Uterine artery pulse index

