### Statistical Analysis

All variables will be compared between case and control groups. Either parametric or nonparametric tests will be applied for continuous variables and *χ*^2^ tests will be used for categorical variables. Receiver operating characteristic analysis will be used when applicable. Univariable or multivariable logistic regression will be applied to develop the prediction models. All *P* values will be two-tailed. The statistical analysis will be run on SPSS version 27 (IBM) statistical software.

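### Chi-square is the only categorical test named for 19 mostly sparse adverse outcomes, and the stated case-control contrast does not address the secondary objective

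*Protocol article*

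**What the plan says.** The secondary objective (Objective section) is to relate the urine misfolded protein level to PE-related maternal or neonatal adverse outcomes. Outcome Measures then gives the list: "maternal death, pulmonary edema, acute renal failure, cerebral hemorrhage, cerebral thrombus, disseminated intravascular coagulation, eclampsia, HELLP syndrome", and so on to periventricular leukomalacia. Counted item by item there are 19, and no composite is named.

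Statistical Analysis states that "All variables will be compared between case and control groups", that chi-square "tests will be used for categorical variables", and that P "values will be two-tailed". It also names ROC analysis where applicable and logistic regression for the prediction models. It names no exact test.

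Selection of Predictor Variables says that "the misfolded protein level in urine will be considered as a predictor candidate for PE onset or adverse outcomes", and adds: "The determination of valid variables will be based on the statistical analysis results with a significance level of" P<.05.

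The inclusion criteria under Recruitment accept, among the features that raise suspicion of PE, "fetal growth restriction, thrombocytopenia" and others. Intrauterine growth restriction is also one of the 19 outcomes.

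**The concern.** Three features of the text do not fit together.

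- **Test and data.** The chi-square approximation needs adequate expected counts. Outcomes such as maternal death or disseminated intravascular coagulation, in about 280 women, will not give them.
- **Comparison and objective.** The one group comparison that is spelled out is by PE status, whereas the objective concerns the misfolded protein result. By PE status, part of the contrast is also true by definition, because pulmonary edema is both a PE criterion (Study Groups section) and a listed outcome.
- **Outcome and entry criterion.** A woman enrolled because of fetal growth restriction already has that outcome, so a urine result at or after entry cannot be said to predict it.

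The abstract's conclusions expect the additional prognostic value of misfolded proteins to be confirmed. An unreliable P value on a sparse outcome, or one from the wrong contrast, could be read as that confirmation.

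**Working it through.** **Inputs.** From Sample Size: 280 evaluable women, 15% test positive, target PPV 54% and NPV 99%, type I error .05. From Outcome Measures: 19 outcomes. Event rates are not in the document; risks of 0.1% to 1% per outcome are assumed.

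**The plan's own figure.** The article gives no figure for the secondary outcomes. The 280 belongs to the primary objective. For one proportion, n = [1.96√(p0(1−p0)) + 0.842√(p1(1−p1))]²/(p1−p0)². This gives 20 test positives for PPV (20/0.15 = 134 in total) and 56 test negatives for NPV (56/0.85 = 66 in total). So 280 is not reproduced as an 80% power figure, but it is more than sufficient. 280/0.94 = 298 agrees with the 300 to be enrolled. None of this bears on the present point; 280 serves here only as the denominator.

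**Group sizes.**
- Test positive: 0.15 × 280 = 42; negative 238.
- Implied PE rate: 0.15 × 0.54 + 0.85 × 0.01 = 8.95%, about 25 cases and 255 controls.

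**Events needed for a smallest expected count of 5.**
- By test result: 5 × 280/42 = 33.3, so 34 events (12%).
- By PE status: 5 × 280/25 = 56 events (20%).

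**One event, in the smaller group.** With group sizes m and N−m, Pearson chi-square = N(N−m)/[m(N−1)] and the Fisher P value = m/N.

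| Split | Pearson chi-square | Pearson P | Yates P | Fisher P | Smallest expected count |
|---|---|---|---|---|---|
| 1/42 vs 0/238 | 280×238/(42×279) = 5.69 | .017 | .33 | 42/280 = .15 | 0.15 |
| 1/25 vs 0/255 | 280×255/(25×279) = 10.24 | .0014 | .15 | 25/280 = .089 | 0.09 |

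At 300 women (1/45 vs 0/255) the P values match the first row. A single event in the smaller group gives uncorrected P<.05 whenever that group has at most 57 of 280 women (20.4%). Both splits lie inside that range.

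**Average type I error per outcome.** This was found by exact enumeration over binomial event counts, with no association and N=280.

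| Assumed risk | Pearson, 42/238 | Fisher, 42/238 | Pearson, 25/255 | Fisher, 25/255 |
|---|---|---|---|---|
| 0.1% | 3.3% | 0.07% | 2.4% | 0.03% |
| 0.2% | 5.1% | 0.2% | 4.4% | 0.1% |
| 0.5% | 6.9% | 0.65% | 7.7% | 0.6% |
| 1% | 6.6% | 1.2% | 7.7% | 1.5% |

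The average is moderate because the rarest outcomes usually have no event at all. The fault shows once an event occurs: with exactly one event and no association, uncorrected chi-square rejects with probability 42/280 = 15% on the test-result split, and Fisher never does.

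**If all 19 were tested separately**, and treated as independent, the chance of at least one false positive would be 1−(1−a)^19. With the sizes above this is 47% to 74% (42/238) or 37% to 78% (25/255) for chi-square, and about 1% to 24% for Fisher. Nineteen tests at exactly .05 already give 1−0.95^19 = 62%.

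**The case against.** A reader might infer that the plan tests all 19 outcomes one by one against the urine result with chi-square at P<.05, and so carries a false-positive risk above 70%. The document does not support that.

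- Chi-square is tied to the comparison of cases with controls. The .05 level is tied to choosing valid predictors, and the outcome list names no test. The list is joined by *or*, which leaves room for an any-event composite.
- The objective concerns a level that is also measured quantitatively. Rank tests, ROC analysis and logistic regression are all named and could serve it without a 2×2 table.
- The single-event result needs the uncorrected Pearson form. The Yates correction removes it, and the article does not say which form is meant.
- Most of the familywise figure is multiplicity. It also assumes independence, although stillbirth overlaps perinatal death, and growth restriction overlaps small for gestational age.
- No event rates are given, and growth restriction, small for gestational age or respiratory distress need not be rare in this population.
- A multiplicity rule, composite definitions and a small-cell fallback may be in the full protocol or SAP, which are not shown.

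All of this stands, and it limits the point. It does not remove what the article itself fixes: one test for all categorical variables, one stated group contrast that is not the contrast in the objective, and an entry criterion that is also an outcome. Logistic regression does not rescue a sparse outcome either. With a zero cell, as in 1/42 vs 0/238, the maximum-likelihood odds ratio is infinite.

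**Conclusion.** The point holds in a limited form. Chi-square without an exact alternative does not suit outcomes with expected counts below 5. Most of the 19 are likely to fall there, since about 34 events are needed by test result and 56 by PE status. The individual P value can be badly wrong (.017 against .15) if the uncorrected form is used, while the average error per outcome stays at about 2% to 8% for assumed risks of 0.1% to 1%. That is not evidence that every stated P value will be wrong. The wider false-positive risk would come from multiplicity, and only if all 19 were tested separately, which the article does not say.

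Two parts need no assumed rate: the case-control contrast does not address the secondary objective, and women enrolled with growth restriction already have a listed outcome. The pulmonary edema overlap is a lesser instance, affecting one outcome in the case-control contrast only. The primary NPV/PPV objective is unaffected. This is a correction worth making to the secondary analyses.

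**What to change.** In Statistical Analysis:

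1. Use Fisher's exact test for any categorical comparison with an expected count below 5.
2. Analyse adverse outcomes by misfolded-protein result rather than by PE status, and say which visit's result is used.
3. Leave women with growth restriction at entry out of the growth-restriction outcome, and report how many are left out.
4. Preferably prespecify one maternal and one perinatal/neonatal composite for the secondary test, with the components reported descriptively with exact confidence intervals.

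The cost is mainly wording. Table 1 already provides for entry criteria and sonographic data at visit 1 and for maternal and neonatal status at delivery and postpartum. The article reports recruitment still open (251 enrolled by March 2024) and analysis not yet started, so on that timetable the change could still be prespecified. The downsides are that composites mix outcomes of different severity, so the components must still be shown, and that the growth-restriction outcome loses some women.

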### Data Collection

Participant data for this study will be collected by investigators and input into an electronic case report form (eCRF). The data will be verified by the principal investigator when suspicious data entries are noted. The data manager will check the completion of the data for final analysis. The study will include 6 visits plus a postpartum documentation. The first visit starts at enrollment, followed by 4 visits once a week when participants come for their routine prenatal examinations. There will be one visit at delivery as well as one postpartum documentation. On occurrence of pregnancy complications, further visits are possible. The clinical data to be collected during each visit are summarized in Table 1. The time interval between two consecutive visits could be 7±2 days, and adherence to the time schedule is crucial for incorporating participant data into the final analysis.

**Table 1 table1:** Summary of the data collection procedure and timeline.

Data collected	Visit 1	Visit 2	Visit 3	Visit 4	Visit 5	Delivery	Postpartum	Unscheduled visit
Inclusion/exclusion criteria	✓							
Informed consent	✓							
General baseline feature	✓							
Chronic history	✓							
Pregnancy history	✓							
Concomitant medication	✓	✓	✓	✓	✓	✓	✓	✓
BMI	✓	✓	✓	✓	✓			✓
Blood pressure	✓	✓	✓	✓	✓		✓	✓
Sampling and detection	✓	✓	✓	✓	✓			✓
Preeclampsia assessment	✓	✓	✓	✓	✓	✓	✓	✓
Laboratory parameters (blood and urine)	✓	✓	✓	✓	✓			✓
Sonographic data	✓	✓	✓	✓	✓			✓
Delivery outcome						✓		
Pregnant woman status						✓	✓	
Fetal/neonatal status						✓	✓	

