**Methods:**

At least 300 pregnant women with clinical suspicion of PE will be enrolled in this prospective cohort study. Participants should meet the following inclusion criteria in addition to a suspicion of PE: ≥18 years old, gestational week between 20+0 and 33+6, and single pregnancy. Consecutive urine samples will be collected, blinded, and tested for misfolded proteins and other PE-related biomarkers at enrollment and at 4 follow-up visits. Clinical assessments of PE status and related complications for all participants will be performed at regular intervals using strict diagnostic criteria. Investigators and participants will remain blinded to the results. Follow-up will be performed until 42 days postpartum. Data from medical records, including maternal and fetal outcomes, will be collected. The performance of urine misfolded proteins alone and combined with other biomarkers or clinical variables for the prediction of PE will be statistically analyzed.

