With increasing knowledge of the condition, six stages of PE have been proposed [6]. Defective placentation (stage 3) results in oxidative stress, and placental-derived products are released into the maternal blood (stage 4) before PE is diagnosed (stage 5). Recently, an increased level of misfolded proteins in the urine has been identified in patients with PE [18], suggesting that PE might share pathophysiologic features with recognized protein misfolding disorders such as Alzheimer disease. In patients with PE, misfolded proteins such as amyloid beta and transthyretin can accumulate in the circulation to exert neurotoxic effects and activate inflammatory cascades, leading to endothelial dysfunction and oxidative stress. Buhimschi et al [18] demonstrated that a dot test using Congo Red, a synthetic diazo dye with specific affinity for misfolded proteins, to visualize this aggregation feature (ie, congophilia) for detecting the presence of misfolded proteins in urine could serve as a promising diagnostic tool for PE. Li et al [19] subsequently developed a simple and rapid point-of-care testing (POCT) tool to detect the presence of misfolded proteins in urine based on visual observation, which achieved an overall sensitivity of 73.6% that reached up to 83% for severe PE cases.

The traditional approach for PE screening is to identify risk factors based on maternal demographic characteristics and medical history; however, this approach can only identify 35% of total PE cases and 40% of preterm PE cases, with a false-positive rate of approximately 10% [20,21]. A noninvasive laboratory method involving measurement of the ratio of soluble FMS-like tyrosine kinase 1 (sFLT-1) to placental growth factor (PlGF) in the urine proved to be effective in PE diagnosis, achieving a sensitivity of 70%-72.5% with a 5%-14% false-positive rate [22,23]. Thus, combining urine PlGF and sFLT-1 testing with other biomarkers may yield the best predictive performance.

In this trial, we will test a new congophilia-based detection method alone or combined with clinical variables and other urine biomarkers to predict the onset of PE before its clinical manifestation. This work can therefore help clinicians better identify PE earlier, enabling the proactive management and monitoring of pregnant women who exhibit signs or symptoms of PE but do not meet the current diagnostic criteria.

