### Objective

The primary objective of this study is to assess the short-term predictive potential of the new congophilia-based detection tool for PE onset in pregnant women with a clinical suspicion of PE. That is, we aim to confirm whether the urine misfolded protein level can be used to rule in or rule out PE in the short term. The secondary objectives are to evaluate whether the urine misfolded protein level correlates with PE-related maternal or neonatal adverse outcomes and to establish an accurate PE prediction model by combining misfolded protein values and multiple indicators.

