### Study Groups: Classification of Cases and Controls

Standard diagnostic criteria [24,25] for PE are new onset of hypertension (systolic blood pressure≥140 mmHg or diastolic blood pressure≥90 mmHg measured on two occasions at least 4 hours apart) and new-onset proteinuria (≥300 mg/day or protein/creatinine ratio ≥0.3 mg/dL) after 20 weeks of gestation. Diagnostic criteria in the absence of proteinuria include any of the following: (1) thrombocytopenia (platelets count<100×10^9^/L); (2) liver function impairment (elevated blood concentrations of liver transaminases to twice the normal concentration); (3) renal insufficiency (serum creatinine>1.1 mg/dL or a doubling of the serum creatinine concentration in the absence of other renal disease); (4) pulmonary edema; and (5) central nervous system abnormalities or visual disturbances.

Cases are defined as patients who develop PE at any time between the first visit to 6 weeks (42 days) postpartum.

Controls are patients who do not develop PE throughout the pregnancy and up to 6 weeks (42 days) postpartum.

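### The case label (PE at any time to 42 days postpartum) and the open sampling schedule do not match the aim of short-term prediction before PE is manifest

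*Protocol article*

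**What the plan says.** The Objective section states: "The primary objective of this study is to assess the short-term predictive potential of the new congophilia-based detection tool for PE onset". It gives no number of days or weeks. The Background says that the test is meant to "predict the onset of PE before its clinical manifestation".

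The outcome and the label carry no time limit. Under Outcome Measures, "The primary outcome is the onset of PE after study inclusion". Under Study Groups, "Cases are defined as patients who develop PE at any time between the first visit to 6 weeks (42 days) postpartum". Each woman therefore has one label.

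The Abstract says that samples are "tested for misfolded proteins and other PE-related biomarkers at enrollment and at 4 follow-up visits". Table 1 marks sampling, blood pressure, laboratory parameters and PE assessment at visits 1 to 5 and also at unscheduled visits. Data Collection says when the latter arise: "On occurrence of pregnancy complications, further visits are possible". Urine Sampling and Storage has every enrolled woman give urine at each visit. No section ends sampling when PE is diagnosed.

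The Statistical Analysis section then says: "All variables will be compared between case and control groups". It names parametric or nonparametric tests, chi-square tests, ROC analysis and logistic regression, without saying which visit's value is used.

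**The concern.** Two things do not fit together.

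First, a comparison by any-time PE answers whether the marker separates women who ever develop PE from those who never do. It does not answer whether a result today rules PE in or out over the coming weeks. A woman whose PE appears months after her last sample counts the same as one diagnosed the following week.

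Second, the schedule yields values taken when PE is being diagnosed, or afterwards. Unscheduled visits, prompted by complications, add samples at just those times. If such values are read as case values, part of the apparent predictive performance is diagnostic performance. This matters most for preset predictors that also belong to the PE criteria. Predictors are retained at P<.05, a rule that favours whichever variables separate the groups most strongly, and values measured at diagnosis will do that.

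At stake is the main claim of the study: the NPV and PPV for rule-out and rule-in, and the composition of the prediction model.

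**Working it through.** **1. The plan's own figure.** The inputs in Sample Size are PPV 54% against 25%, NPV 99% against 90%, positive test rate 15%, alpha .05, power 80% and dropout 6%. Statistical Analysis makes P values two-tailed. With one result per woman,

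n = [z(1−α/2)·√(p0(1−p0)) + z(0.80)·√(p1(1−p1))]² / (p1−p0)².

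- PPV: (1.960×0.433 + 0.842×0.498)² / 0.29² = 19.1 positives; 19.1/0.15 gives 128 women (exact binomial: 174).
- NPV: (1.960×0.300 + 0.842×0.0995)² / 0.09² = 55.7 negatives; 55.7/0.85 gives 66 women (exact binomial: 64).

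The stated 280 is not reproduced, but it exceeds every requirement, so calling it sufficient is correct. 280/0.94 = 298, in line with at least 300. At 280, exact joint power for both targets is 96.0% (two-sided). The calculation counts women, so one index sample per woman leaves its unit unchanged.

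**2. Sampling span against label window.** Visits 1 to 5 have four intervals of 7±2 days: 4×5 = 20 to 4×9 = 36 days. The label runs to 42 days after delivery. Assuming delivery at 40+0:

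- entry at 20+0: 140 + 42 = 182 days;
- entry at 33+6: 280 − 237 = 43 days, and 43 + 42 = 85 days.

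Even for the latest entrant, the label extends well beyond the last scheduled sample.

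**3. Samples around diagnosis.** A woman diagnosed at visit 2 has one scheduled sample before that visit (visit 1) and up to four at or after it (visits 2 to 5), plus any unscheduled sample.

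**4. Predictors that overlap the diagnosis.**

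| Preset predictor (Textbox 2) | Diagnostic criterion (Study Groups) |
|---|---|
| Blood pressure | Hypertension threshold |
| Proteinuria | Proteinuria threshold |
| Serum creatinine | Renal insufficiency |
| Aspartate aminotransferase | Liver transaminases |

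Values from before diagnosis are legitimate predictors. At diagnosis they help to define the outcome.

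**5. How far a few cases move the result.** Implied prevalence is 0.15×0.54 + 0.85×0.01 = 8.95%, or 25.06 cases in 280. With 42 positives and 238 negatives, true positives are 42×0.54 = 22.68 and false negatives 238×0.01 = 2.38. Assume that five of the true positives were positive only in samples at or after diagnosis. On pre-diagnosis samples:

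- PPV = 17.68/37 = 47.8% (from 54%);
- NPV = 1 − 7.38/243 = 97.0% (from 99%);
- sensitivity = 17.68/25.06 = 70.6% (from 22.68/25.06 = 90.5%).

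The five are an illustration; the article gives no figure for them.

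**The case against.** The strongest reply is that this is a condensed article and the analysis plan is not shown. The choice of index sample, the handling of samples after diagnosis and the unit of analysis are commonly settled there. A collection schedule does not say what is used for prediction, and samples taken at diagnosis may serve the secondary objectives. The Background's own wording points to pre-diagnosis use, and excluding confirmed PE at entry makes visit 1 a usable pre-diagnosis sample. Data Collection also calls adherence to the time schedule crucial for entering the final analysis, which may mean that off-schedule samples are left out.

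Much of this stands. The absence of a named index sample would not be a finding by itself. The adherence sentence cuts both ways, since it also suggests that the follow-up visits are meant to be analysed. What the reply does not remove is that this article fixes a label without a horizon, and a comparison by that label, for an objective that is short-term.

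A reader might infer more than the text supports:

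- That repeated samples are pooled as if independent. Statistical Analysis does not say so, Sample Size counts participants and Study Groups classifies patients. Pooling is a risk only, because no repeated-measures method is named.
- That sampling after diagnosis is stated. It follows from the schedule but is not said outright.
- That the article concedes that diagnostic accuracy does not carry over to prediction. Study Implications says only that such a failure is possible.

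**Conclusion.** The concern holds as a mismatch between the objective and the stated rules. An any-time label, read against sampling that ends 20 to 36 days after enrolment, does not test short-term prediction. No stated rule keeps values measured at or after diagnosis out of the predictive analysis, and four preset predictors overlap the diagnostic criteria.

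The size cannot be read from the document. With about 25 expected cases, a handful of reclassified results is enough to move PPV by about 6 points and sensitivity by about 20. That rests on the plan's assumed rates and the illustrative five cases. The 85 to 182 day window rests on delivery at 40 weeks.

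The verdict does not depend on pooling, and it does not challenge the figure of 280. It should be resolved before analysis, which the Results section places after follow-up is complete.

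**What to change.** Specify before analysis:

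1. The visit 1 sample is the primary index sample, one per woman.
2. Predictive claims, including those for blood pressure and laboratory predictors, use only values taken before the date on which PE criteria are met. Same-day, later and complication-triggered samples are reported separately as diagnostic accuracy.
3. The primary analysis labels women by PE within a prespecified short-term window chosen by the sponsor. PE at any time to 42 days postpartum is kept as secondary.
4. If visits 2 to 5 are also used for prediction, fit a visit-level model with woman-clustered errors or GEE.

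The article gives no horizon for its NPV and PPV targets, so the sponsor should state that they refer to the chosen window.

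The cost is analysis specification and programming, with no new data and no change to care. The downside is that some samples, and cases arising after the window, leave the primary analysis, so it will rest on fewer than the roughly 25 cases implied for any-time PE if that figure was meant for the whole follow-up.

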### Sample Size

The target negative predictive value (NPV) is 99% and the target positive predictive value (PPV) is 54.0%. A positive test rate of 15% is assumed. The Type I error is set to .05. A sample size of 280 should be sufficient to detect NPV>90% and PPV>25% with 80% power. Therefore, at least 300 eligible participants will be included in this study considering a dropout rate of 6%. To avoid an overrepresentation of cases of late-onset PE, no more than 50% of the enrolled participants will be at 32 weeks gestation or above and no less than 20% of the enrolled participants will be at gestational week below 28+0 at inclusion.

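### The Data Collection sentence on visit timing can be read as making entry to the final analysis depend on events after baseline, which conflicts with the case definition and primary outcome and risks selection bias in PPV and NPV

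*Protocol article*

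**What the plan says.** Under Data Collection, the Protocol article describes the visits as follows: "The first visit starts at enrollment, followed by 4 visits once a week when participants come for their routine prenatal examinations". It adds that "The time interval between two consecutive visits could be 7±2 days" and that "adherence to the time schedule is crucial for incorporating participant data into the final analysis". It states no number of windows that may be missed and no exception for PE, admission or delivery before Visit 5. It does not say whether an off-window sample or the whole woman would be left out. The same section also says that "On occurrence of pregnancy complications, further visits are possible", and Table 1 has an unscheduled-visit column with sampling and PE assessment.

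Three other statements bear on who is analysed:

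- Study Groups: "Cases are defined as patients who develop PE at any time between the first visit to 6 weeks (42 days) postpartum". Controls are the women who stay free of PE over the same period.
- Outcome Measures: "The primary outcome is the onset of PE after study inclusion".
- Sample Size: "at least 300 eligible participants will be included in this study considering a dropout rate of 6" per cent. Exclusion for visit timing is not mentioned there.

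**The concern.** The stated aim is short-term rule-in and rule-out of PE. A woman who develops PE in the first weeks is an informative case for that aim, and also one of the women least likely to complete four regular weekly intervals. Delivery can intervene too: up to half the cohort may enter at 32 weeks or later, and for entry between 32+0 and 33+6 the nominal Visit 5 falls at 36+0 to 37+6 weeks.

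If the schedule sentence is applied to whole women, membership of the analysis set depends partly on the outcome being predicted. PPV and NPV both depend on the mix of cases and controls analysed, so they would move for reasons unrelated to the test. The prediction question itself needs only a valid index urine and a known PE status. Table 1 schedules PE assessment at delivery, postpartum and at unscheduled visits, so status can be known without on-time weekly attendance.

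The wording also leaves the choice between dropping samples and dropping women open until the data are in hand.

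**Working it through.** **1. The statements side by side**

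| Section | What decides inclusion or classification | Schedule condition? |
|---|---|---|
| Data Collection | Adherence to 7±2 day intervals | Yes, extent unspecified |
| Study Groups | PE status, first visit to 42 days postpartum | None |
| Outcome Measures | PE onset after inclusion | None |
| Sample Size | 6% dropout | Not mentioned |

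Take a woman diagnosed between Visits 2 and 3 who does not attend Visits 4 and 5. She is a case under Study Groups and has the primary outcome under Outcome Measures. Under a literal reading of Data Collection her data may not enter the final analysis.

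**2. The plan's own figures**

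Inputs from Sample Size: "The target negative predictive value (NPV) is 99% and the target positive predictive value (PPV) is 54.0" per cent; positive rate 15%; null values NPV 90% and PPV 25%; power 80%; 280 evaluable; 6% dropout; at least 300 enrolled.

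- Dropout step: 280/0.94 = 297.9, so 298. This agrees with at least 300.
- The 280 itself is not reproduced. An exact binomial test of PPV with 15% of N positive needs about N = 144 (one-sided 5%) or N = 170 (two-sided 5%) for 80% power. At N = 280 there are 42 positives and PPV power is 97% (two-sided) or 99% (one-sided); NPV power exceeds 99.9%. The method behind 280 is not given. That is a separate matter and does not support this point; it matters here only because it shows slack.

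**3. Expected cases**

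Implied PE prevalence = 0.15×0.54 + 0.85×0.01 = 0.081 + 0.0085 = 8.95%. In 300 women:

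- true positives 300×0.081 = 24.3; false positives 300×0.15×0.46 = 20.7
- false negatives 300×0.0085 = 2.55; true negatives 300×0.85×0.99 = 252.45
- cases 24.3 + 2.55 = 26.85, about 27

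**4. Effect of losing cases**

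Assume a fraction f of cases is lost whatever their test result, and no controls. Then PPV = 24.3(1−f)/[24.3(1−f) + 20.7] and NPV = 252.45/[252.45 + 2.55(1−f)]. The documents give no value for f, so a range is shown.

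| f | PPV | NPV | Women lost, share of 300 |
|---|---|---|---|
| 0 | 54.0% | 99.0% | 0 |
| 10% | 21.87/42.57 = 51.4% | 99.1% | 2.7 (0.9%) |
| 25% | 18.225/38.925 = 46.8% | 99.2% | 6.7 (2.2%) |
| 50% | 12.15/32.85 = 37.0% | 99.5% | 13.4 (4.5%) |

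The reverse case: if 25% of controls and no cases were lost, PPV = 24.3/(24.3 + 15.525) = 61.0% and NPV = 189.34/(189.34 + 2.55) = 98.7%.

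**5. The 6% allowance and power**

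The allowance leaves 300×0.94 = 282. Suppose all four windows must be met and on-time attendance is independent with probability q per interval, so the share kept is q⁴. Staying within 6% needs q ≥ 0.94^(1/4) = 0.985; keeping 280 needs q ≥ (280/300)^(1/4) = 0.983. At q = 0.98, 0.95 and 0.90 the numbers left are 277, 244 and 197. All values of q are assumptions.

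With PPV and positive rate unchanged, exact two-sided 5% PPV power is 93% at N = 244 and 91% at N = 197, and stays at or above 80% down to about N = 170, a loss of 130/300 = 43%. Loss of cases alone would exceed 6% (18 women) only if more than 18/26.85 = 67% of expected cases went.

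**The case against.** The strongest reply is that no exclusion rule is written. *Crucial* may be an instruction on conduct, and participant data may mean the data from a given visit, so that only off-window samples are dropped. Study Groups and Outcome Measures point towards keeping early cases, unscheduled sampling is planned, and all women are followed to 42 days postpartum. A journal article may also leave analysis sets to a document not shown. What stands of this is that whole-woman exclusion is one reading, not a stated fact. What does not stand is that this is merely missing detail: the article itself links schedule adherence to entry into the final analysis, and that link conflicts with its own definitions if followed literally.

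A reader might infer that the rule breaks the 6% allowance or leaves the trial underpowered. The documents do not support either. They give no adherence rate; the losses in step 5 need a strict four-window, whole-woman, independent-attendance rule, and clustering of on-time attendance within women would leave more of them for the same q. Falling below 280 would not by itself lose the stated 80% power.

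A reader might also infer that the rule mainly flatters NPV. Under loss of cases NPV barely moves, while PPV falls, which works against the test's rule-in claim. If women with milder courses skip visits, the loss of controls pushes both measures the other way. The net direction is therefore unknown.

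**Conclusion.** The point holds as a risk of selection bias created by a stated sentence that conflicts with other sections. Its size depends on how many women the sentence would remove and which ones, and the documents do not say. Under the design's own figures, if a quarter of cases and no controls were lost, PPV would shift by about 7 percentage points (54.0% to 46.8%) and NPV by 0.2 (99.0% to 99.2%). This rests on the target PPV, NPV and positive rate being true and on case loss being unrelated to the test result.

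The 6% allowance does not visibly cover schedule exclusions, but no breach is shown, and this is not a power problem. The sentence should be changed, because the correction is simple and the possible distortion falls on both target measures.

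**What to change.** Reconcile Data Collection with Sample Size, Study Groups and Outcome Measures:

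- Define the primary analysis set as all eligible enrolled women with a valid Visit 1 urine result and known PE status, regardless of the timing of later visits.
- Use the actual date of each sample.
- Apply the 7±2 day window only to label samples in visit-specific summaries.
- Report an on-schedule-only analysis as a sensitivity analysis.

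Visit timing then no longer removes women, and the 6% is not asked to absorb schedule exclusions. The cost is wording, plus slightly noisier visit timing in the repeated-sample analyses. The article reports that analysis waits for complete follow-up and that test results are kept apart from the case report forms, so the change can be made before results are seen.
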